#### Data analysis

Statistical analyses will be performed using a per protocol analyses. The primary endpoint in this study is live birth rates in both treatments. Since intention-to-treat analyses is more adequate for implementing the results of this study in daily fertility practice such an analyses will be performed also besides a per-protocol analysis. Using logistic regression analysis confounding factors will be analyzed. These factors include age during initial treatment, duration of the subfertility, number and quality of the embryos transferred and outcome of initial treatment. Selection of these criteria is based on current opinion in literature
[20-24]. A comparison of baseline characteristics of enrolled patients with the baseline characteristics of patients who refused enrollment will be performed to exclude selection bias.

Secondary endpoints are clinical and ongoing pregnancy rates, cancellation rate, endometrium thickness and (serious) adverse events. Most secondary endpoints will be analyzed using a Fishers’ exact test; endometrium thickness will be analyzed using a student *t*-test. Cost-efficiency of both treatments will be calculated on the ratio between differences in cost and live birth rates.

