**Methods and design:**

In this randomized, multi-centre, non-inferiority trial we aim to test the hypothesis that there is no significant difference in live birth rates between patients undergoing NC-FET versus AC-FET. The primary outcome will be live birth rate per embryo transfer procedure. Secondary outcomes will be ongoing and clinical pregnancy rate, cancellation rate, (serious) adverse events and cost-efficiency. Based on a live birth rate of 20% and a minimal clinical important difference of 7,5% (one-sided alpha 2,5%, beta 20%) a total of 1150 patients will be needed. Analyzes will be performed using both per protocol as well as intention to treat analyses.

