## Background

In Vitro Fertilization (IVF) or Intra Cytoplasmatic Sperm Injection (ICSI) treatment cycles often produce more embryos than can be transferred during the fresh treatment cycle. Moreover, in some patients embryo transfer is postponed for medical reasons (e.g. ovarian hyperstimulation syndrome). Cryopreservation of these embryos provides both physicians and patients a safe, successful and presumably cost-efficient option
[1-3]. Recent development and implementation of single embryo transfer strategies in IVF and IVF -ICSI programs has increased the importance of successful frozen thawed embryo transfer (FET) programs. Critical for a successful FET program is synchronization between the endometrial development and the embryo
[4-7]. To achieve this, FET requires extensive preparation, timing and planning. In recent years, several methods for endometrium preparation have been developed.

In natural cycle FET (NC-FET) planning of embryo thawing and transfer requires the identification of a period of optimal receptivity
[4-7]. This putative ‘window of implantation’ starts shortly after ovulation. If an embryo is transferred within this window, the chances of conceiving are greater
[4-6]. Planning NC-FET can either be done based on recognition of the LH surge that precedes ovulation (using serum or urine LH monitoring) or by triggering ovulation (sometimes referred to as modified NC-FET). Using modified NC-FET, the development of the dominant follicle is closely monitored by regular ultrasonic evaluation. On reaching a diameter of 16-20 mm human chorionic gonadotrophin (hCG) is administered and ovulation takes place approximately 36 h later. Embryo thawing and transferring can be planned accordingly. Despite ultrasonic monitoring, spontaneous ovulations do occur. In such an event the start of the window of implantation cannot be estimated accurately. Since identification of the onset of the window of implantation is mandatory for further timing of FET, cycles with spontaneous ovulation are usually cancelled. To minimize cancellation, patients are required to visit their clinic several times which is time consuming and expensive. In NC-FET cycles, 5-6% of all patients have insufficient development of the dominant follicle and/or endometrium thickness and treatment has to be cancelled

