### Primary and secondary endpoints

The primary endpoint is live birth rate per FET. Secondary endpoints are cancellation rate, clinical pregnancy rate, ongoing pregnancy rate (all per FET), endometrium thickness during transfer and (serious) adverse events. More over cost-efficiency calculations will be performed.

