### Interventions

#### NC-FET (intervention 1)

Patients allocated to intervention 1 will undergo their FET in a natural cycle. Starting on day 10, 11 or 12 of their cycle regular ultrasonic evaluation of the endometrium thickness and mean diameter of the dominant follicle is performed. When the endometrium is 6 mm or more and the diameter of the dominant follicle is 16-20 mm a blood sample is taken (for blinded analyses of progesterone and LH levels) and ovulation is induced using hCG injection (pregnyl 5000 IE, MSD USA or ovitrelle 250 μgram, Serono Benelux bv, Germany). Thawing and transferring is performed subsequently according to local protocols. A maximum of two embryos will be transferred.

If during ultrasonic evaluation no follicle is visible ovulation is deemed to have occurred. In this event no thawing or transferring will take place. This cycle is regarded a drop-out. Further treatment can be conducted according to local protocols (Figure
2).

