#### AC-FET (intervention 2)

If patients are allocated to intervention 2, an artificial cycle FET will be performed. From day one of the cycle patients commence oral estradiol (progynova, Bayer, Germany) 2 mg three times daily. After 11, 12 or 13 days an ultrasound is performed. If no leading follicle is present and the endometrial thickness is ≥ 8 mm, micronized progesterone (utrogestan Besins International, Belgium) is added to the regime and thawing and transferring is commenced 4 or 5 days later according to the stage of cryopreservation
[20].

If the endometrial thickness is less than 8 mm, the progynova dose is raised to 2 mg 4 times daily for 7 days. After a week the endometrium is checked once again. When the endometrium thickness is >8 mm and no dominant follicle (≥ 14 mm) is present, utrogestan can be added and thawing and transferring is performed according to local protocols. A maximum of two embryos will be transferred.

If a follicle is visible during ultrasound, serum luteinizing hormone (LH) and progesterone levels are determined. If these are raised, (serum LH ≥ 13 E/l or progesterone ≥ 15 nmol/l) luteinization of the follicle is considered to have taken place and because of the associated diminished pregnancy rates, thawing and transferring will not be performed. If serum levels are below the above mentioned levels thawing and transferring can be performed according to local protocol (Figure
3).

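### The plan leads with per-protocol and adds intention-to-treat without saying which decides non-inferiority, and the leading analysis appears to drop cycles cancelled because of the allocated strategy

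*Protocol article*

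**What the plan says.** The Data analysis section of the protocol article opens with "Statistical analyses will be performed using a per protocol analyses". It then describes intention-to-treat as better suited to daily practice and says that "such an analyses will be performed also besides a per-protocol analysis". The abstract lists the two without order: "Analyzes will be performed using both per protocol as well as intention to treat analyses". Neither place says which analysis decides, or that both must meet the margin.

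The endpoint section states "The primary endpoint is live birth rate per FET", and the abstract "The primary outcome will be live birth rate per embryo transfer procedure". The sample-size section gives the expected 20% live birth rate per cycle.

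On natural cycles in which ovulation has already occurred, the NC-FET section says: "In this event no thawing or transferring will take place. This cycle is regarded a drop-out". For artificial cycles with a luteinised follicle, the AC-FET section says that "thawing and transferring will not be performed". Cancellation rate is a secondary endpoint. The article does not define the per-protocol set.

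**The concern.** Cancellation happens after randomisation and partly because of the strategy assigned. A missed ovulation is a way in which natural-cycle preparation fails. A luteinised follicle is a way in which artificial-cycle preparation fails. Neither is a departure from the protocol, since in both cases the protocol itself directs that no transfer takes place. If such cycles leave the leading analysis, the arms are compared among women selected by how their strategy performed, and the protection of randomisation is lost.

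Two things are at stake. First, a difference per transfer can fall inside the margin while the difference per randomised woman does not, or the reverse. Second, if the two analyses disagree, nothing in the article says what the trial concludes.

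**Working it through.** **Inputs from the article.** AC-FET live birth rate 20%; margin 7.5 points; one-sided alpha 2.5%; 1150 patients allocated 1:1, so 575 per arm; NC-FET as the arm tested for non-inferiority (Study design section).

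**The plan's own figure.** A standard non-inferiority calculation gives n per arm = (1.960 + 0.842)² × 2 × 0.20 × 0.80 / 0.075² ≈ 447, or 894 in total. The stated 1150 is not reproduced from the stated inputs. That is a separate matter; 575 per arm is taken as given here.

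**Assumed inputs.** Cancellation rates c_NC and c_AC. The Background offers one figure: "In NC-FET cycles, 5-6% of all patients have insufficient development of the dominant follicle and/or endometrium thickness". It does not cover cancellation for spontaneous ovulation, and no AC rate is given. The rates are therefore varied in both directions.

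**Method.** Set the truth at the margin per randomised woman: 12.5% NC v 20% AC. A non-inferiority claim is then false for that question and should occur 2.5% of the time. Now analyse only cycles with a transfer:

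- rates r_NC = 0.125/(1 − c_NC) and r_AC = 0.20/(1 − c_AC), with d = r_NC − r_AC
- numbers 575(1 − c) in each arm
- SE = √[r_NC(1 − r_NC)/n_NC + r_AC(1 − r_AC)/n_AC]
- P(claim) = 1 − Φ(1.96 − (0.075 + d)/SE)

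**Worked case, NC 20%/AC 10%.** r_NC = 0.1563 and r_AC = 0.2222, so d = −0.0660. The numbers are 460 and 517.5, and SE = 0.0249. Then (0.075 − 0.0660)/0.0249 ≈ 0.36, and P = 1 − Φ(1.60) = 0.055.

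| NC cancelled | AC cancelled | d per transfer (points) | False claim, formula | False claim, simulation |
|---|---|---|---|---|
| 0% | 0% | −7.5 | 2.5% | 2.6% |
| 6% | 3% | −7.3 | 3.0% | 3.1% |
| 10% | 5% | −7.2 | 3.5% | 3.6% |
| 6% | 0% | −6.7 | 5.5% | 5.6% |
| 20% | 10% | −6.6 | 5.5% | 5.5% |
| 15% | 5% | −6.3 | 7.0% | 7.1% |
| 25% | 10% | −5.6 | 11.5% | 11.4% |
| 5% | 5% | −7.9 | 1.6% | 1.7% |
| 10% | 10% | −8.3 | 1.0% | 1.1% |
| 20% | 20% | −9.4 | 0.4% | 0.4% |
| 5% | 10% | −9.1 | 0.4% | 0.4% |

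The simulation used 400,000 runs per row. The all-randomised analysis stayed at 2.5% to 2.6% in every row.

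**Where the direction turns.** The rate is 2.5% when d = −7.5 points, that is when 0.125/(1 − c_NC) = 0.20/(1 − c_AC) − 0.075. With AC at 5% this gives c_NC = 1 − 0.125/0.1355 ≈ 7.8%. With AC at 10% it gives 1 − 0.125/0.1472 ≈ 15.1%. NC cancellation must exceed AC by roughly half again before the error rises.

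**Requiring both analyses to pass.** The false-claim rate is at most about 2.6% in every simulated scenario. When the arms are truly equal at 20% per randomised woman and per-protocol still drops cancelled cycles, power is 88.9% with no cancellation, 82.5% at 10% in each arm, 74.7% at 20% in each arm, 88.9% at NC 20%/AC 10%, and 41.1% at NC 10%/AC 20%.

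**The case against.** Leading with per-protocol and adding intention-to-treat is usual in a non-inferiority trial. A reader might infer that the order is itself an error. It is not, and calling intention-to-treat better suited to practice explains why it was added rather than contradicting the plan.

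A reader might also infer that the trial's type I error is inflated. The documents do not support that. On the endpoint as worded in the abstract, per transfer procedure, a true difference of −6.6 points is inside the margin, so a claim there is correct. The error appears only if the question is live birth per randomised woman, and only if NC-FET cancels sufficiently more often. The Background leans that way: it names unexpected ovulation as an NC-FET risk and reports a claim that oestrogen lowers cancellation. But the endometrial thickness criterion is 6 mm in NC-FET and 8 mm in AC-FET, which could push the other way. With equal or higher AC cancellation, the per-transfer test is conservative.

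Nor is it certain that cancelled cycles leave the per-protocol set. That is inferred from the drop-out wording, used for one NC event only, and from the per-transfer denominator. A full protocol or SAP may define the set. Cancellation is also reported openly as a secondary endpoint.

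These points limit the size and direction of the concern. They do not remove it. The article itself chooses the analyses, puts per-protocol first and words the denominator, and followed as written this leaves the deciding comparison open. The denominator is also not settled: the endpoint section counts cancellation per FET too, which makes sense only if FET means a started cycle, and the sample-size section speaks of cycles.

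**Conclusion.** The point holds as a gap in the decision rule, combined with a leading analysis that appears to exclude strategy-caused failures. It should be settled before the data are analysed. For live birth per randomised woman, the false-claim rate of the per-transfer comparison runs from 0.4% to 7.0% in the main scenarios (NC 5%/AC 10% to NC 15%/AC 5%), and to 11.5% at NC 25%/AC 10%, against a nominal 2.5%. At modest differences such as 6% v 3% the excess is small, about 3.0%. These figures rest on assumed cancellation rates, on the inferred exclusion of cancelled cycles, and on taking the randomised woman as the unit of interest. Neither the direction nor the size can be fixed from the documents. For that reason the rule needs to be set before it is known which analysis is the more favourable.

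**What to change.** In the Data analysis section, state that:

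- live birth is analysed per randomised woman, with a cancelled cycle counted as no live birth;
- non-inferiority is concluded only if the 95% confidence interval excludes a 7.5-point deficit for NC-FET in both the all-randomised and the per-protocol analyses;
- cancellation under the protocol's own rules is not a per-protocol exclusion.

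Align the denominator in the abstract and in the Primary and secondary endpoints section, and keep the per-transfer rate as a secondary result.

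No new data are needed, since all patients take part with one cycle and cancellations are already recorded. The costs are a small loss of power from requiring both analyses and a real change of the primary denominator from per transfer to per randomised woman. The third clause keeps the power loss small: without it, the both-must-pass rule falls to 82.5% power at 10% cancellation in each arm and to 41.1% at NC 10%/AC 20%.

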### Study population and recruitment

Patients participating in the ANTARCTICA trial are between the age of 18 and 40 and are undergoing FET after their 1^st^, 2^nd^ or 3^rd^ IVF or IVF-ICSI cycle for various indications. They must all have ovulatory cycles between 26 and 35 days and be willing to give written informed consent to participate in the study.

Those patients who have a known contra-indication or allergy for oral estradiol or vaginally administered micronized progesterone are not eligible. Patients with a uterine anomaly are also excluded from participation. Oocyte donation for any other than a genetic indication is also an exclusion criterion.

Eligible patients are informed about the ANTARCTICA trial during intake by their physician prior to FET cycle. A minimum reflection period of 5 days will be offered. Eligible patients who wish to participate will be randomized after providing written consent. If an eligible patient declines participation, some basic characteristics will be obtained to identify any significant selection bias.

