### Data collection

Data collection is performed using a web-based case report form (electronic CRF or eCRF). Basic data on patient’s general history and specific fertility history are obtained from the out-patient clinic chart. Characteristics of the initial treatment as well as characteristics of the FET treatment are also noted.

For the cost-efficiency study patients are invited to answer a web-based questionnaire after completing treatment.

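### The logistic regression adjusts for number and quality of embryos transferred, which are fixed after randomisation and are not baseline confounders

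*Protocol article*

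**What the plan says.** The Data analysis section promises a per-protocol and an intention-to-treat analysis and then states: "Using logistic regression analysis confounding factors will be analyzed". The factors named are age at initial treatment, duration of subfertility, and "number and quality of the embryos transferred and outcome of initial treatment". It does not say whether this model is primary or supportive, which analysis set it is fitted to, or how women without a transfer enter it.

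The order of events is given elsewhere. Under Study population and recruitment: "Eligible patients are informed about the ANTARCTICA trial during intake by their physician prior to FET cycle", and "Eligible patients who wish to participate will be randomized after providing written consent". Under NC-FET (intervention 1), after monitoring and hCG: "Thawing and transferring is performed subsequently according to local protocols. A maximum of two embryos will be transferred". If ovulation is deemed to have occurred: "In this event no thawing or transferring will take place". The AC-FET section has the same limit on number, but its own endometrial criterion for proceeding and its own reason for withholding thawing, namely raised LH or progesterone.

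On what is recorded, Data collection says: "Characteristics of the initial treatment as well as characteristics of the FET treatment are also noted".

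**The concern.** A confounder of a randomised comparison would have to precede allocation. Age, duration of subfertility and outcome of the initial treatment do. Number and quality of the embryos transferred do not: they are settled at transfer, after the arms have been prepared, timed and cancelled under different rules, and by clinic staff who can hardly be unaware of the regimen. (The Study design section claims blinding only for the research team.)

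Two things could follow. First, if the arm influences what is transferred, conditioning on it removes that part of the effect. It can also introduce bias through unmeasured prognosis that affects both the embryos transferred and live birth. Second, quality is undefined without a transfer, so a standard fit silently restricts the model to women who had one. In a non-inferiority trial, an adjusted estimate that hides a deficit could be read as support for non-inferiority.

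**Working it through.** **Timing of each covariate against randomisation**

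- Age at initial treatment, duration of subfertility, outcome of initial treatment: known before randomisation.
- Number transferred: decided at transfer, one or two, after randomisation.
- Quality of embryos transferred: defined only once embryos have been thawed and selected, after randomisation.

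**Can the arm affect them?** The documents give routes but no evidence of size. The endometrial criterion differs (6 mm or more in NC-FET, 8 mm in AC-FET). The reason for no transfer differs. The timing of thawing differs (local protocols after hCG, against 4 or 5 days after progesterone is added). Cancellation rate is itself a secondary endpoint.

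**Illustration of mediation (all inputs assumed).** Let logit P(live birth) = -1.8 + 0.8 × good quality, with no direct effect of arm.

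- Poor quality: 1/(1 + e^1.8) = 14.2%. Good quality: 1/(1 + e^1.0) = 26.9%. Gap: 12.7 points.
- With 50% good-quality transfers: 0.5 × 14.2 + 0.5 × 26.9 = 20.5%, close to the article's 20%.
- Share falls from 50% to 40% in NC-FET: -0.10 × 12.7 = -1.3 points.
- Share falls from 50% to 30%: -0.20 × 12.7 = -2.5 points.
- Effect within quality level: 0 in both cases, by construction.

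For scale, the margin is 7.5 points.

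**Separating the two mechanisms.** This is a simulation of 400,000 women with live birth of about 20% per transfer, an unmeasured prognostic factor, and no direct arm effect. All inputs are assumed. Shift means lower number and quality transferred in NC-FET.

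| No transfer, NC / AC | Shift | Difference, all randomised (points) | OR, all randomised | OR adjusted for number and quality | Women used |
|---|---|---|---|---|---|
| 6% / 6% | no | 0.0 | 1.00 | 1.00 | 94% |
| 6% / 6% | yes | -1.6 | 0.90 | 1.02 | 94% |
| 20% / 10% | no | -2.0 | 0.87 | 1.00 | 85% |
| 20% / 6% | no | -2.9 | 0.82 | 1.00 | 87% |
| 20% / 6% | yes | -4.1 | 0.75 | 1.03 | 87% |

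Row 1 shows no bias when cancellation is equal and the covariates are unaffected. Row 2 isolates the covariate problem. In rows 3 and 4 the gap comes entirely from leaving out women without a transfer. Row 5 combines both.

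**Women lost in a complete-case intention-to-treat fit.** Lost = 1150 × c, where c is the overall no-transfer rate. The only figure in the article is 5-6% in NC-FET for insufficient follicle or endometrium (Background). Applied overall, as an assumption: 1150 × 0.05 = 57.5, about 58; 1150 × 0.06 = 69. Spontaneous ovulation would add to this, and no AC-FET rate is given. The total of 1150 is taken as stated; this point does not depend on its derivation.

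**The case against.** **Role of the model.** The article does not call the logistic model primary, and the 7.5-point margin is an absolute difference, whereas a logistic model yields an odds ratio. Nothing ties the non-inferiority test to this model. This stands. A reader might infer that the adjustment tilts the trial's main conclusion towards non-inferiority, but the documents do not support that.

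**Loss of women without a transfer.** A reader might also infer that the covariate list is what removes every such woman. The article does not say so. The primary outcome is already counted per transfer procedure, so in that analysis these women are absent with or without the embryo covariates. This also stands. The covariates cause the loss only if the model is fitted to all randomised women.

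**Mechanism.** The embryos were frozen before the arms diverge, both arms have the same maximum of two, and quality is recorded to common study criteria. A shift in what is transferred is possible, through timing or an unblinded choice of number, but it is not documented. The quality shifts used above are invented for illustration, the null adjusted effect is built in, and a shift in the other direction would reverse the bias.

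**Cancellation rate.** An overall rate of 15-20% (173 to 230 women) might be supposed, but it has no source in the article.

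None of this makes post-randomisation variables legitimate confounders. It limits the size, direction and severity of the point.

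**Conclusion.** The covariate list is wrong for a treatment-effect model. Two of the named factors are fixed after randomisation and cannot confound the comparison. This is an explicit statement in the article, not a detail left to an analysis plan.

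The size of any bias is unknown. It arises only if the arms differ in what is transferred or in who reaches transfer, and its direction is not guaranteed. On the assumed inputs, total effects of -1.3 to -2.5 points vanish after adjustment, at most about a third of the margin (2.5 / 7.5 = 0.33). The loss of 58 to 69 women depends on two conditions: an intention-to-treat fit restricted to complete cases, and the 5-6% figure holding overall.

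The point should be fixed. It is not critical, because the role of the model is not stated and the main test may not use it.

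**What to change.** State that the adjusted treatment-effect model uses only factors known at randomisation: age, duration of subfertility, outcome of the initial treatment, the IVF/IVF-ICSI stratum and clinic. Add number and quality of embryos cryopreserved if these are recorded. Keep all randomised women in the intention-to-treat model, counting no transfer as no live birth from that cycle. Report any model containing embryos transferred only as a labelled exploratory or sensitivity analysis, with number and quality transferred described by arm. State also whether the logistic model is primary or supportive.

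The cost is a change of wording, best made before outcome data are seen; the sample size does not change. One item needs checking: the article says that characteristics of the initial treatment are noted but does not itemise them, so it is not confirmed that the eCRF captures the number and quality of cryopreserved embryos. If it does not, the remaining factors suffice.

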[19]. If live birth rates indeed are equal in NC-FET and AC-FET the perceived burden of both treatments, convenience and cost-efficiency might be important factors in choosing one of both options.

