### Hypothesis

The hypothesis to be tested is that there is no significant difference in live birth rates between NC-FET and AC-FET, but that NC-FET is more cost effective. Since the expected low incidence of serious adverse events we expect to find no significant difference based on a type 1 error.

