### Study design

The ANTARCTICA trial is a multi-center, randomized controlled trial, powered to demonstrate non-inferiority of NC-FET in terms of the primary study end point. A recent systemic review of current literature identified no other RCTs addressing this subject. Several retrospective studies have shown discrepant findings but pooling of the data indicated no difference in pregnancy rates between NC-FET and AC-FET. Since our hypothesis is that significant difference in the primary study endpoint will not be observed, but a difference in cost-efficacy in favour of the NC-FET will be demonstrated, a non-inferiority design is appropriate. The research team is blinded for the result of the randomization (Figure
1).

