### Statistical analysis

#### Sample size and power considerations

Live birth rates in FET treatment in the Netherlands are, on average, 20% per cycle. The minimal clinical important difference (MCID) could not be based on literature concerning FET treatment alone. Based on other studies within fertility care a consensus of a MCID of 7,5% was adapted. This clinical important difference compares to a one sided hypothesis test with a 0.025% significance level with a null hypothesis of AC-FET being inferior to NC-FET. Using a two-sided alpha of 5% and 80% discriminating capacity we calculated that 1150 patients have to be enrolled in this study. All patients will participate with one cycle only.

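### The planned cost-efficiency ratio divides by a live-birth difference that the trial expects to be near zero, so taken alone it is a poor basis for calling NC-FET more cost effective

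*Protocol article*

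**What the plan says.** The Data analysis section gives the economic analysis one sentence: "Cost-efficiency of both treatments will be calculated on the ratio between differences in cost and live birth rates". Read naturally, this is an incremental ratio, with the cost difference over the live-birth difference.

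The Hypothesis section pairs two statements: "no significant difference in live birth rates between NC-FET and AC-FET, but that NC-FET is more cost effective". The Study design section uses the same pairing to justify the design: "a difference in cost-efficacy in favour of the NC-FET will be demonstrated, a non-inferiority design is appropriate". The Background motivates the economic comparison by the case of equal outcomes: "If live birth rates indeed are equal in NC-FET and AC-FET", burden, convenience and cost may decide the choice.

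The sample-size section supplies the live-birth assumption, "Live birth rates in FET treatment in the Netherlands are, on average, 20% per cycle", and a total of 1150 patients. Allocation is 1:1 (Randomization section). The article states no cost figures.

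**The concern.** An incremental cost-effectiveness ratio is readable when the effect difference is clearly away from zero. Here the effect difference is the quantity that the trial presumes to be close to zero. If that premise is right, three problems follow.

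- The sign of the ratio is set largely by chance in the live-birth counts, even if the cost saving is known perfectly.
- Its size swings widely, because a small denominator magnifies any saving.
- A negative value is ambiguous. It arises when NC-FET is cheaper and better, and equally when it is dearer and worse.

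The claim at stake is half of the stated hypothesis and part of the reason given for a non-inferiority design. The named statistic is least informative in exactly the situation that the trial expects.

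**Working it through.** **Inputs.** Live birth 20% in both arms (sample-size section, applied to both arms under the hypothesis); 1150 patients at 1:1, so 575 per arm. Every patient is taken to contribute an outcome; fewer would make the denominator noisier. The saving of 100 units and the willingness-to-pay values below are assumptions.

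**The plan's own figure.** The article gives no number for the economic analysis. Its 1150 is taken as stated. It does not follow from the stated inputs: (1.960 + 0.842)² × 0.32 / 0.075² = 446.5, so 447 per arm and 894 in total. That is a separate matter. At 447 per arm the standard error below would be larger, √(0.32/447) = 2.68 points.

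**Standard error of the denominator.** √(2 × 0.2 × 0.8 / 575) = √(0.32/575) = 0.0236, or 2.36 points; the 95% half-width is 1.96 × 2.36 = 4.6 points.

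**Sign of the denominator.** Two independent binomial(575, 0.20) counts, summed exactly at a true difference of zero:

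| Observed live-birth difference | Share of trials |
|---|---|
| Positive | 48.5% |
| Negative | 48.5% |
| Exactly zero (ratio undefined) | 2.9% |
| Within ±0.5 point | 14.6% |

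The last row covers count differences of -2 to +2, since 0.005 × 575 = 2.9 births. Each of these five values has probability of about 2.9%.

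**Interval for the ratio.** A Fieller 95% set is bounded only if the denominator differs from zero at the two-sided 5% level, that is if |d|/SE > 1.96. The exact probability that it is not bounded is:

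| True live-birth difference | Fieller set unbounded |
|---|---|
| 0 | about 95% |
| 1 point | about 93% |
| 2 points | about 86% |

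At a true difference of 1 point, the observed difference still has the wrong sign in about 32% of trials.

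**Size of the ratio.** Live births are counts, so the smallest non-zero difference is 1/575 = 0.174 point. For a fixed saving of 100, the largest absolute ratio is 100 / (1/575) = 57,500 per live birth. A difference of +1 birth and one of -1 birth each occur in about 2.9% of trials, or 2.9/97.1 = 3.0% of those in which the ratio is defined. That exceeds 2.5% in each tail, so the 2.5th and 97.5th percentiles are these extremes: -57,500 and +57,500. One birth either way moves the result from one end, through undefined, to the other.

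**A summary that stays defined.** Incremental net monetary benefit is λ × (live-birth difference) − (cost difference), with λ the willingness to pay per live birth. With a saving of 100, a zero live-birth difference and cost variance ignored, it equals 100, with 95% half-width 1.96 × λ × 0.0236:

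| λ (assumed) | Half-width |
|---|---|
| 1,000 | 46 |
| 5,000 | 231 |
| 10,000 | 462 |

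This shows openly how the live-birth uncertainty weighs on the economic claim as λ rises.

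**The case against.** The strongest reply is that the article condenses a fuller plan. The ratio is a customary headline in trial-based economic evaluation, and interval methods, a cost-effectiveness plane or net benefit may well be specified elsewhere. That stands as far as missing detail goes, and none is held against the article here. It does not cover the choice of the ratio as the stated measure, which the article itself makes.

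Second, the hypothesis speaks of no significant difference, not of a difference of zero. That is correct, and the 95% figure belongs to exactly zero. But 1 or 2 points is still less than one standard error, and the ratio fares little better there.

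Third, the sentence might be loose wording for cost per live birth within each arm. That denominator would be stable: 20% with a standard error of √(0.16/575) = 1.67 points. The reference to differences makes the incremental reading the more natural one. If the arm-wise ratio is meant, the text should say so.

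Fourth, calculating the ratio requires both components, and looking at them resolves the sign ambiguity. This stands. A reader might infer that the trial cannot support the cost-effectiveness claim at all. The documents do not support that: the weakness is in the ratio taken alone, and nothing says that it will be reported alone or formally tested. Nor does any passage exclude the costs of cancelled cycles.

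**Conclusion.** The point holds for the ratio as the stated economic measure. Under the article's own premise its denominator is centred near zero with a standard error of 2.36 points, its sign is close to a coin toss, and a Fieller set would be unbounded in about 95% of trials (about 86% at a true 2-point difference). It is therefore a poor basis, taken alone, for the claim "but that NC-FET is more cost effective". The cost and live-birth data to be collected can support that claim through a better summary.

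These figures rest on 20% in both arms and 575 analysed per arm. The ±57,500 range rests also on the assumed, perfectly known saving of 100 and scales in proportion to it; the sign instability does not depend on it. A reader who models the denominator as continuous normal might infer a wider range, or a ratio without finite mean or variance. Neither carries over to counts: at a fixed saving the ratio is bounded, and undefined only when the difference is exactly zero.

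The primary endpoint, the sample size and the non-inferiority conclusion are not affected. The change should be made because the economic claim is part of the stated hypothesis.

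**What to change.** Restate the economic analysis in the analysis plan before outcome data are examined:

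- Main result, part one: the mean cost difference per woman randomised, with a bootstrap 95% confidence interval.
- Main result, part two: incremental net monetary benefit over a stated range of willingness to pay per live birth, from a joint bootstrap of costs and live births that resamples women within arm so that the two outcomes stay paired.
- Supplementary: the ratio, shown only as a point on the cost-effectiveness plane beside its two components.

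The cost is a short change of wording and standard bootstrap code on the data already planned, with no extra patients. The one real demand is that the investigators must choose and justify a willingness-to-pay range, which the ratio let them avoid.
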